#### Sham acupuncture group (shown in Fig. 2 and Table 1)

The sham acupuncture group will be given sham therapy with the same treatment duration and frequency of sessions as the real acupuncture group. Based on previous clinical experience, we chose acupoints that are ineffective in treating insomnia for the sham acupuncture group. The following acupoints will be punctured in the sham group: Binao (LI-14), Shousanli (LI-10), Yangchi (TE-4), Waiguan (TE-5), Fengshi (GB-31), Liangqiu (ST-34), and Futu (ST-32). The same needle size as in the real acupuncture group will be used. Unlike the real acupuncture application, needles will be inserted superficially 1 mm without manual stimulation. The needles will be kept in place for 30 min. Meanwhile, creation of the De qi sensation will be prevented by not manipulating the needles.

#### Healthy control group

No acupuncture intervention will be conducted in the healthy control group.

### Functional MRI scanning procedure

The rs-fMRI data will be obtained with a Siemens TRio 3.0 Tesla MRI scanner in Beijing Hospital of Traditional Chinese Medicine. All rs-fMRI images will be taken from a contiguous echo planar imaging template under the following conditions: 33 axial slices, repetition time = 2000 ms, echo time = 30 ms, thickness/gap = 3.5/0.6 mm, field of view = 220 × 220 mm^2^, flip angle = 90°, and matrix size 64 mm × 64 mm with 240 volumes. All participants will receive the following instructions: stay awake, do not move, close your eyes, and do not try to think about anything. For an anatomic reference, T1 images will be obtained before resting state scans.

The real acupuncture and sham acupuncture groups will be examined three times (before treatment, after treatment, and in the follow-up period.) and the healthy controls will be examined only once.

### Follow-up procedure

Eight weeks after the end of treatment, the PSQI, fMRI, FS-14, HAS, HAMD, actigraphy, and sleep diary records will be collected.

### Outcome measurements

Figures 1 and 2 show all outcome parameters.

### Primary outcome

Primary outcome is the mean change in PSQI scores from baseline to the end of the treatment period. The PSQI, a self-assessment questionnaire to evaluate sleep quality, will be the primary outcome measurement [25]. The PSQI contains 19 items consisting of seven component scores, including sleep quality, sleep latency, sleep duration, daytime dysfunction, sleep efficiency, sleep disturbances, and sleeping medication. Higher global scores reflect worse sleep quality [26].

### Secondary outcomes

#### Sleep diaries

Sleep diaries will be assessed for sleep quality [27]. Participants with insomnia disorder will be required to record their bedtime, sleep time, wake-up time, sleep latency, the state after morning awakening, and related factors in their sleep diaries. Recording of sleep diaries will be performed at baseline and at 4 and 12 weeks following entry into the study.

#### Hyperarousal scale

The HAS is a self-evaluation questionnaire containing 26 items. The questionnaire will be employed to evaluate the behaviors of cortical arousal, including information processing, strong response to unexpected stimuli, and introspective tendencies [28]. The scores correlate positively with a heightened arousal state. This questionnaire is usually applied to measure the change in increased cortical responsiveness [29].

#### Fatigue scale-14

Fatigue is a dominant effect of insomnia [30]. The FS-14 is a self-rating scale to measure the severity of physical and mental fatigue. The FS-14 scores correlate positively with fatigue severity.

#### HAMD and HAMA

Assessment of depressive status will be made with the HAMD. The HAMD is comprised of 17 variables with five- or three-point scales. Scores will be interpreted as follows: less than 7, normal; 8 to 17, mild depression; 17 to 24, moderate depression; and 24 or over, severe depression [31].

The 14-item HAMA will be used to determine anxiety. The HAMA is comprised of a 14-point self-assessment questionnaire, with a five-point scale for each item. A normal score is less than 7, scores between 7and 14 suggest mild anxiety, scores between 14 and 20 indicate moderate anxiety, scores between 21 and 28 indicate severe anxiety, and a score greater than or equal to 29 indicates extremely severe anxiety [32].

For patients with insomnia disorder, the scores for HAMD and HAMA will be collected at baseline, week 4, and at the 8-week follow-up. The HAMD and HAMA will be collected only once at baseline in the healthy control group. Collection of the week-long sleep diaries will be at baseline, at 4 weeks after treatment, and at the end of the 8-week follow-up.

#### Actigraph

To obtain objective data on sleep and activity, we will request that participants wear an actigraph (MTI Health Services Company, Pensacola, FL, USA) on their nondominant wrist for three 1-week periods (before the intervention, at the end of the intervention period, and at the end of the follow-up period) [33].

#### Safety monitoring

Potential adverse events from acupuncture include fainting, needle sticking, infections at the puncture site, and subcutaneous hematoma. Participants will be asked to report adverse events, and practitioners will report any adverse events at each patient visit. Vital signs and adverse events will be chronicled in the case report form at each visit. There is no anticipated harm and no compensation for trial participation.

#### Quality control

To ensure a standard operation procedure, acupuncturists will consistently apply acupuncture with the correct acupoints and manipulation. Investigators will attend training to properly apply the randomization number table, to make the diagnoses, to understand the inclusion and exclusion criteria, and to complete the case report forms. In addition, the fMRI scan will be performed with the same scanner and operator. Patients will be asked to close their eyes during the entire scanning procedure and stay still but not sleep.

Additionally, the Scientific Research Supervision group of the Beijing Hospital of Traditional Chinese Medicine will monitor the study regularly to ensure adequate recruitment rate, data accuracy, and data validity.

### Statistical analysis

#### Clinical data analysis

Statistical analyses will be performed with Statistical Package for the Social Sciences (version 19.0) based on the intention-to-treat principle. Two-sided tests will be considered significant at 5%. We will investigate the reasons for any missing data and, if necessary, multiple imputations will be applied. Data will be evaluated in agreement with the intention-to-treat principle. Sociodemographic information will be shown as the mean ± standard deviation or the frequency (%) when appropriate. The baseline continuous, dependent variable data will be compared using independent-sample *t* tests and chi-square tests will be performed for categorical data. Differences between group means will be analyzed with a repeated-measures analysis of variance. Multivariate analysis of variance will be performed and Bonferroni correction will be applied for pairwise comparisons of changes in questionnaire scores with repeated measurement times for each group.

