### Trial design

This study will be conducted as a single-center, prospective parallel group, patient- and assessor-blinded, randomized controlled trial. The trial will be conducted in accordance with the Consolidated Standards of Reporting Trials [18] and Standards for Reporting Interventions in Clinical Trials of Acupuncture principles [19] to fulfill adequate reporting standards for randomized controlled trials. Sixty patients with insomnia disorder will be assigned to either a real acupuncture group or a sham acupuncture group, using a digital randomization table in a 1:1 ratio. Participants will keep a sleep diary at baseline, during week 4 of treatment, and during week 8 of the follow-up period. Both the neuropsychological measurements and fMRI scans will be performed at baseline, after completion of the acupuncture treatments, and at the conclusion of the follow-up period. Thirty age- and sex-matched healthy individuals who sleep well will be recruited as controls for the fMRI data analysis. All outcome measures will be performed once for the healthy control patients (Fig. 1).

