### Sample size

This study aims to determine the efficacy and central mechanism by which acupuncture affects insomnia disorder. Based on our previous pilot study [20], the PSQI score significantly decreased by 4.43 ± 3.60 in the group treated with acupuncture compared to 1.30 ± 2.58 in the control group. Based on a power analysis, 26 patients per group were required to detect a significant difference (power = 0.9, α = 0.05, two-sided). Thus, we plan on recruiting 30 patients per group to compensate for a 15% drop out rate. There is no known sample size calculation for fMRI research. However, for the exploratory study, 15 to 30 patients are adequate to test the null hypothesis [21, 22].

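### The only named between-group analysis can discard an observed week-4 PSQI when week 12 is missing, and imputation is left to judgement after the fact

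*Protocol article*

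**What the plan says.** The Primary outcome section sets the endpoint: "Primary outcome is the mean change in PSQI scores from baseline to the end of the treatment period". Treatment lasts 4 weeks, so the endpoint needs two PSQI values, baseline and week 4.

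PSQI is nevertheless collected three times. Under Trial design, the neuropsychological measurements are "performed at baseline, after completion of the acupuncture treatments, and at the conclusion of the follow-up period", and the Follow-up procedure adds: "Eight weeks after the end of treatment, the PSQI, fMRI, FS-14, HAS, HAMD, actigraphy, and sleep diary records will be collected". The last visit is therefore week 12 (4 + 8).

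For the between-arm comparison, Clinical data analysis says: "Differences between group means will be analyzed with a repeated-measures analysis of variance". A multivariate ANOVA with Bonferroni-corrected pairwise comparisons over the repeated measurement times follows. The t tests and chi-square tests in that section are for baseline data. No separate week-4 analysis of PSQI is named, and the visits entering the ANOVA are not listed.

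On missing data the section says "We will investigate the reasons for any missing data and, if necessary, multiple imputations will be applied". It commits to intention-to-treat twice, the second time as "Data will be evaluated in agreement with the intention-to-treat principle".

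**The concern.** A classical repeated-measures ANOVA, like a multivariate ANOVA on the same visits, uses only patients with a value at every visit in the model. The measurement schedule, the reference to repeated measurement times, and the weight the Discussion puts on long-lasting effects all make a three-visit model the natural reading. In such a model without imputation, a patient who completes treatment, gives the week-4 PSQI and then misses week 12 is left out of the arm comparison, although the primary endpoint was observed.

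The imputation clause does not rule this out. It is conditional, it follows an investigation of the missing data, and no condition is given, so the set of patients behind the primary test can be settled after the pattern of missingness is known.

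Two things are at stake. Some primary data that were collected may go unused. The primary comparison may also be conditioned on an event after the endpoint, attendance at week 12, which matters if attendance depends on how well the patient responded.

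**Working it through.** **Inputs (Sample size section).** The pilot result is "the PSQI score significantly decreased by 4.43 ± 3.60 in the group treated with acupuncture compared to 1.30 ± 2.58 in the control group". The requirement is "26 patients per group were required to detect a significant difference (power = 0.9, α = 0.05, two-sided"). Recruitment is 30 per group, to allow for 15% dropout.

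**The plan's own figure.**
- Difference: 4.43 − 1.30 = 3.13.
- Root-mean-square SD: √((3.60² + 2.58²)/2) = √9.808 = 3.13, so d = 1.00.
- Normal formula: n = 2(1.960 + 1.282)² × 9.808/3.13² = 21.04, so 22 per group. The exact t calculation gives 23.
- With the larger SD of 3.60 in both arms: 28 (normal) or 29 (t).

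The stated 26 is not reproduced. It is conservative against 22–23 and does not affect this point. For dropout, 26/0.85 = 30.6 (31) and 26 × 1.15 = 29.9 (30), so the stated 30 is close either way.

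**How many observed week-4 values could be lost.** 15% of 30 is 4.5 per arm, leaving 25.5 with complete data. The documents do not say when dropout occurs, so the range is:

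| Assumed timing of the 15% | With week-4 PSQI, per arm | Complete at week 12, per arm | Observed week-4 values at risk, per arm |
|---|---|---|---|
| All before week 4 | 25.5 | 25.5 | 0 |
| Constant rate over 12 weeks | 28.42 | 25.5 | 2.92 |
| All in follow-up | 30 | 25.5 | 4.5 |

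Middle row: 1 − 0.85^(1/3) = 0.0527; 30 × 0.0527 = 1.58 leave by week 4; 4.5 − 1.58 = 2.92 leave later.

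**Precision.** The standard error of the week-4 difference grows by √(28.42/25.5) = 1.056 in the middle row and √(30/25.5) = 1.085 in the last row.

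**Power for the week-4 difference of 3.13 (exact t, two-sided 5%).**

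| Per arm analysed | SD 3.13 | SD 3.60 |
|---|---|---|
| 30 | about 97% | 91% |
| 28 | 96% | 89% |
| 26 | 94% | 87% |
| 25 | 93% | 85% |

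In the worst row of the timing table, power falls from about 97% to 93–94% with the pilot SDs, or from 91% to 85–87% with SD 3.60.

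**Bias, as illustration only.**
- *Strong assumption.* Take constant-rate dropout and suppose that late leavers had a mean change of 0 in both arms. They are 2.92/28.42 = 10.3% of patients with week-4 data. If the difference among all patients with week-4 data is 3.13, the complete cases show 3.13/0.897 = 3.49, which is 0.36 or 11% too large.
- *Milder assumption.* In a simulation of 3,000 trials per setting, the chance of follow-up dropout rose smoothly as the week-4 improvement fell, by the same rule in both arms. With a 15% dropout probability at the average improvement, the mean difference was 3.12 from all week-4 values and 3.12 from complete cases. With 25% it was 3.14 and 3.20.
- *Unrelated to response.* Dropout independent of response produced no bias beyond simulation error.

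**The case against.** A reader might infer that the plan removes every patient who leaves during follow-up, or that deletion is its default. The text does not support that. It lists no visits for the ANOVA, excludes no one, invokes intention-to-treat twice and provides for multiple imputation, which would keep these patients. The conditional clause may mean no more than that imputation is used if data are missing. An ANOVA on baseline and week 4 alone would also fit the wording and lose no follow-up leaver. The consent form described under Participants and recruitment asks whether data may be used after withdrawal, which points towards retention. All of this stands, and it limits the point to what can happen.

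A reader might also take 3.49 as the expected result. It is not. It needs a three-visit model, no imputation, an assumed dropout timing and zero response in every late leaver. Nothing in the documents shows that late leavers are non-responders, and a milder dependence gives almost no bias.

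It can be added that the precision loss is already budgeted, since 25.5 complete patients per arm is close to the planned 26. That is correct for power. It does not answer the question of which patients are analysed.

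Finally, a journal article may leave the imputation trigger and the model's visits to a fuller document. That would settle a bare omission. Here the article does name a method and a conditional rule, and together they do not guarantee that the stated primary endpoint is analysed on all patients in whom it was observed.

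**Conclusion.** The point holds as a gap in protection for the primary comparison. A complete-case method is the only between-group clinical analysis named, a later visit that the endpoint does not need may enter it, and whether imputation prevents the loss is decided after the missing data are seen, without a criterion.

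The size is modest. If the 15% allowance is right, between 0 and about 4 to 5 observed week-4 values per arm are at risk, and the power cost is at most about 3 to 4 percentage points with the pilot SDs. No estimate of bias can be drawn from the documents: it may be nil, and its size depends on how late dropout relates to response in each arm. The stronger reason to act is that an intention-to-treat primary comparison should not depend on attendance eight weeks after its endpoint. The change is worth making; the point does not show that the trial's result would be invalid.

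**What to change.** In Clinical data analysis, name the primary analysis explicitly: the between-arm difference in PSQI change at week 4, estimated from all randomised patients with an observed week-4 value, whether or not they attend week 12. Either of two methods is enough:

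- a likelihood-based mixed model for repeated measures, with arm, visit, their interaction and baseline PSQI, reporting the week-4 contrast; or
- an ANCOVA of week-4 PSQI adjusted for baseline.

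Replace the conditional imputation clause with a fixed rule. For example, missing week-4 PSQI is handled by the mixed model, and multiple imputation of all randomised patients is the prespecified sensitivity analysis. If the ANCOVA is chosen, state that multiple imputation is always applied to missing week-4 values. The week-12 comparison can then be reported as a secondary result.

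The cost is wording: the same data, visits, sample size and software. The Trial status section reports recruitment as still open with six participants enrolled, so on that account the rule could be fixed before outcome data are seen.

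### The repeated-measures ANOVA is not tied to the primary outcome: no effect, time point or baseline adjustment is named for the end-of-treatment PSQI comparison

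*Protocol article*

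**What the plan says.** The Primary outcome section fixes a single quantity: "Primary outcome is the mean change in PSQI scores from baseline to the end of the treatment period". The Sample size section rests on a pilot in which "the PSQI score significantly decreased by 4.43 ± 3.60 in the group treated with acupuncture compared to 1.30 ± 2.58 in the control group", and concludes that "26 patients per group were required to detect a significant difference", at power 0.9 and two-sided 5%.

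PSQI is measured three times. Trial design says the neuropsychological measurements "will be performed at baseline, after completion of the acupuncture treatments, and at the conclusion of the follow-up period", and Follow-up procedure confirms PSQI at the last visit: "Eight weeks after the end of treatment, the PSQI, fMRI, FS-14, HAS, HAMD, actigraphy, and sleep diary records will be collected".

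Under Clinical data analysis, the between-group method is one sentence: "Differences between group means will be analyzed with a repeated-measures analysis of variance". A multivariate analysis of variance follows, and "Bonferroni correction will be applied for pairwise comparisons of changes in questionnaire scores with repeated measurement times for each group". Baseline appears only in a comparison of the arms: "The baseline continuous, dependent variable data will be compared using independent-sample *t* tests". No deciding effect, set of visits, primary contrast or baseline covariate is named.

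**The concern.** A repeated-measures ANOVA with two groups and three visits yields several tests that answer different questions.

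- **Group main effect.** This compares the arms on the average over visits. If baseline is one of the visits, it brings in a true difference of zero, because the arms are randomised, and so dilutes the effect.
- **Overall group-by-time F test.** This has 2 degrees of freedom and responds to any divergence between the arms, including one that appears only at follow-up.
- **Baseline-to-end-of-treatment part of the interaction.** Only this matches the declared outcome, and the text does not select it.

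The pairwise comparisons do not settle the matter, since their wording reads most naturally as comparisons over time within each arm. What is at stake is which p-value counts as the trial's result, and whether it has the power the sample size was meant to buy.

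**Working it through.** **Inputs from the protocol.** Mean PSQI decrease 4.43 (SD 3.60) against 1.30 (SD 2.58); two-sided 5%; power 0.90; 26 per arm; three visits.

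**Assumptions, because the article gives no figures.** The pilot change refers to end of treatment. The three visits have equal variance and equal correlation ρ, with ρ = 0.3, 0.5 or 0.7. A fraction f of the effect is kept at follow-up (f = 1 sustained, 0.5 half, 0 faded).

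**1. The plan's own figure.** Difference 4.43 − 1.30 = 3.13. Pooled SD of change = √[(3.60² + 2.58²)/2] = √9.808 = 3.132. Then n = 2(1.960 + 1.282)² × 9.808/3.13² = 21.04, so 22 per arm (23 with the t distribution). The stated 26 is larger, hence on the safe side. At 26 per arm the t test on change has noncentrality 3.13/(3.132√(2/26)) = 3.60 and power 0.94.

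**2. Visit SD.** The change SD fixes σ = 3.132/√[2(1 − ρ)] = 2.65, 3.13, 4.04 for ρ = 0.3, 0.5, 0.7.

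**3. Three-visit group main effect.** Expected difference = 3.13(1 + f)/3. SD of a patient's mean = σ√[(1 + 2ρ)/3] = 1.93, 2.56, 3.62. Example, ρ = 0.5 and f = 1: 2.087/(2.557√(2/26)) = 2.94, power 0.82.

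| Effect at follow-up | ρ = 0.3 | ρ = 0.5 | ρ = 0.7 |
|---|---|---|---|
| Sustained | 0.97 | 0.82 | 0.53 |
| Half kept | 0.82 | 0.58 | 0.33 |
| Faded | 0.48 | 0.30 | 0.18 |

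**4. Overall group-by-time F (2 and 100 df).** Noncentrality = (26/2) × Σ(δⱼ − mean δ)²/[σ²(1 − ρ)], where δⱼ is the group difference at visit j and σ²(1 − ρ) = 9.808/2 = 4.904 for every ρ.
- Sustained (0, 3.13, 3.13): 13 × 6.531/4.904 = 17.3, power 0.96.
- Half kept (0, 3.13, 1.565): 13 × 4.898/4.904 = 13.0, power 0.90.
- Faded (0, 3.13, 0): 17.3, power 0.96.
- Follow-up only (0, 0, 3.13): 17.3, so significant about 96% of the time, while the end-of-treatment change test is significant about 5% of the time.

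**5. Leaving the choice open.** If there is no effect and either the main effect or the interaction may count as success, the chance of a false positive is about 1 − 0.95² = 0.0975 (0.097 by simulation). If either the end-of-treatment or the follow-up change may count, simulation gives about 0.09.

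**6. A named, baseline-adjusted end-of-treatment contrast.** Residual SD = σ√(1 − ρ²) = 2.52, 2.71, 2.89; power at 26 per arm 0.99, 0.98, 0.97. The variance relative to the change score is (1 + ρ)/2, that is 0.65 to 0.85.

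**The case against.** The strongest reply is that the stated model contains the right test. Restricted to baseline and end of treatment, the group-by-time test is algebraically the t test on PSQI change. A condensed article may leave the choice of contrast to an analysis plan that is not shown. This stands in part: a reader might infer that the planned ANOVA cannot test the primary outcome, and that would be wrong. But the article is not silent. It names a method over three visits, and that method as written does not lead to the outcome in its own Primary outcome section.

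Four further readings go beyond the text:

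- **Baseline is ignored.** Not so: it is one of the repeated measurements. Only covariate adjustment is unnamed, and the unadjusted change score already exceeds the planned 90%.
- **Power is lost.** This is conditional. The interaction test keeps about 0.90 to 0.96, and the main effect keeps 0.97 at ρ = 0.3 with a sustained effect.
- **Patients with a missed visit are dropped.** The article states no complete-case rule. It invokes intention-to-treat and allows multiple imputation.
- **Within-arm tests will be used to claim efficacy.** The article does not say so, and its hypothesis is worded as acupuncture against sham.

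It is also fair that an effect appearing only at follow-up is not something the documents predict, and that it would be a real group difference. The scenario shows only that the overall F test does not isolate the end of treatment. Finally, the Sample size section names neither a test nor a time window, so its link to the end-of-treatment change is inferred from the figures.

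**Conclusion.** The point holds as a mismatch between sections: the named analysis is not tied to the declared primary outcome or to the change-score difference behind the sample size, and no baseline adjustment is named. How much this costs depends on which effect decides. With the three-visit main effect, power at 26 per arm is 0.82 (sustained) or 0.58 (half kept) at ρ = 0.5, and runs from 0.97 to 0.33 across ρ = 0.3 to 0.7 for those two patterns; it is lower still if the effect fades. With the overall interaction, power is adequate, but significance need not reflect the end of treatment. The correlations, equal-correlation structure and follow-up effects are assumptions. The mismatch itself does not depend on them.

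**What to change.** State one primary test: the between-group difference in end-of-treatment PSQI, adjusted for baseline PSQI, two-sided 5%, reported with a 95% confidence interval. Either an ANCOVA or the week-4 contrast of a mixed model using all available post-baseline values, with baseline as covariate, would serve. Make the follow-up comparison secondary, and label within-group comparisons over time as descriptive.

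The cost is a few sentences in the statistical section. All the data are already scheduled for collection, and 26 per arm remains enough. The article reports recruitment as ongoing, so the change can be made, dated and recorded before anyone is unblinded.
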